## Methods/design

### Setting and participants

Family physicians will be recruited over a six month period from seven community areas (Figure 1) within the city of Winnipeg, Manitoba, Canada. Winnipeg is the capital city of the province with a population of approximately 685,000 (half the population of the province). In order to be eligible for the study, FPs must be in regular family practice (full or part-time), fee-for-service, solo or group practice and may be a member of the Physician Integrated Network and/or Uniting Primary Care and Oncology Network (Table 1). Once a family physician/medical clinic has agreed to participate in the study, a Family Physician/Clinic Characterization Form (Additional file 2) will be completed to document the routine care provided by each family physician in regards to CRC screening practices with the FOBT, whether they utilized an electronic medical record, have an on-site laboratory, and to document any additional information necessary to ensure minimal intrusiveness of the study protocol in the daily functioning of the clinical practice. Each family physician will enroll 30–35 patients who are: (1) attending their periodic health exam; (2) considered at average risk of developing colorectal cancer (Table 2); and (3) provide informed consent to participate. A patient tracking form (Additional file 3) will be filled out by the family physician for each patient enrolled.

**Figure 1 F1:**
[figure not shown]
**The 12 community areas of Winnipeg, Manitoba, Canada. **The seven community areas represented in the study protocol include St. James-Assiniboia, Assiniboine South, Downtown, River Heights, St. Boniface, St. Vital, and Fort Garry. These represent those areas not yet involved in the province’s colorectal cancer screening program.

**Table 1 T1:** Description of stratification criteria Used in randomizing medical clusters to study groups

**Stratification criteria**	**Description**
**Physician Integrated Network (PIN) **[30]	A Manitoba Health primary care renewal initiative that focuses on fee-for-service (FFS) physician groups.
	Its goal is to facilitate systemic improvements in the delivery of primary care.
	Objectives:
	● To improve access to primary care
	● To improve Primary Care Providers’ access to and use of information
	● To improve the work life for all primary care providers
	● To demonstrate high quality primary care with a specific focus on Chronic Disease Management
**Uniting Primary Care and Oncology Network (UPCON)**[31]	A collaborative partnership between Winnipeg family practice clinics/primary health care centres and CancerCare Manitoba (CCMB) that is dedicated to promoting and supporting the shared care of the cancer patient.

**Table 2 T2:** Patient eligibility criteria

**Inclusion criteria**	**Exclusion criteria**
Attending for a Periodic Health Examination	Walk-in patients
Males and females 50 to 74 years of age	Having had a colonoscopy in the last 10 years
No symptoms of colorectal cancer	Having had a flexible sigmoidoscopy within the last 5 years
No personal history of CRC, polyps, or diseases of the colon requiring monitoring by colonoscopy (Crohn’s Disease or Ulcerative Colitis)	Having a double contrast barium enema within the last 5 years
Have a first degree relative with CRC affected at age greater than 60	
Have two or more second degree relatives with polyps or cancer	

From our initial recruitment efforts, we determined that there were three methods by which patients receive an FOBT. Most FPs provide a laboratory requisition form to patients who are then given the test kit by laboratory staff. Alternatively, the FPs support staff may provide the FOBT kit directly to patients (with a requisition attached) or the FP may give the FOBT Kit directly to their patients (with a requisition attached). All FPs will continue with their current practice which will be documented. Whether kit distribution method affects patient FOBT uptake will be assessed. The rationale for customizing this portion of the study protocol is to optimize FP collaboration (recruitment) and to simulate “real world” clinical practice. Hence, the study findings will be relevant to practitioners and more likely used to make evidence-based decisions that are translated into practice.

### Sample size determination, randomization, and statistical analysis

Individual randomization of physicians within a group-practice and individual patients to either the control or intervention arm of the study is not feasible [32]. A cluster randomized design was chosen in which family physicians within a group practice were randomized to the same experimental group (control or intervention) and considered a cluster. Randomization of clusters will be conducted by a biostatistician using a computer-generated list and all of a physician’s patients will receive the same experimental treatment (control or intervention). Our protocol defines a multi-level analysis facilitating analysis of the intraclass correlation coefficient (ICC) for each primary group-level outcome (patients, FP, clinics/clusters) [32]. To ensure an even distribution of cluster-level characteristics between experimental groups, clusters will be randomized within strata based on membership in the Physician Integrated Network (PIN) and/or Uniting Primary Care Oncology Network (UPCON) [28]. These represent two quality improvement initiatives in Manitoba (Table 2). Clusters will be block randomized based on the number of collaborating FPs within a practice. An absolute increase in FOBT screening rates of 15% from the current 42% in Manitoba will be considered clinically significant [14]. Sample size was determined by a biostatistician using PASS (Power and Sample Size, 2002) software and a computer simulated ICC value of 0.6 [33] taking into consideration the clustered design of the trial [34]. This is a very conservative estimate of the minimum detectable effect size (MDEF) given the proposed sample size. Based on logistic regression a cluster size of 41 clusters each enrolling 30 to 35 patients (of which 80% are in the group that does not utilize the supplied intervention/magnet and 20% are in the group that does utilize the intervention/magnet; 1230 observations) will achieve 90% power at a 0.05 significance level to detect a change from the baseline value of 0.400 to 0.550 and corresponds to an odds ratio of 1.833. In the event that family physician collaboration/retention and/or patient recruitment proves to be more difficult than anticipated, a logistic regression with a cluster size of 28 (840 observations) achieves 80% power with the same outcomes.

Research has shown a majority of patients completing the FOBT do so within 4 to 6 weeks [20]. In order to allow adequate time to complete the FOBT and return it to the laboratory, patients will be given four months to do so. Those patients not returning their FOBT test within a period of four months will be scored as failing to complete the FOBT test.

Analysis of results will be based on the intention to treat (ITT) model. All Statistical analysis will be performed using SAS 9.2 ® software. Categorical variables will be compared using the Chi-square test. The time taken to return FOBT cards will be analyzed with Cox’ Proportional Hazards Regression analysis. Due to the clustered design, study outcomes will be measured at the level of the patient, family physician, and medical clinic/cluster. The analysis will utilize multi-level logistic regression that accounts for variance among patients with the same FP, FP within the same cluster, and among the clusters. The SAS® GLIMMIX procedure will be used to model patient FOBT completion rate (response variable). This will enable evaluation of the rate of patient FOBT compliance within medical clusters and individual FPs. Sources of variance included in the model will include cluster level (treatment, electronic medical record or paper charts, PIN and/or UPCON membership), family physician level (gender, solo/group practice), and patient level (age, gender, socioeconomic status, and previous FOBT screening history) variables as well as random variation.

A computerized randomization number list will be used to select 10 patients per FP to be contacted for a Post-Study Follow-Up Survey (Additional files 4 and 5) conducted by telephone. Only those patients providing permission to be contacted will be included. Those patients surveyed will be asked for permission to document their Personal Health Identification Number which will facilitate future studies conditional to Health Research Ethics Board (HREB) approval of analysis of repeat colorectal cancer screening behavior over time.

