**Methods/design:**

A pragmatic, two-arm, randomized cluster controlled trial conducted in 22 community-based family practice clinics (36 clusters) with 76 fee-for-service family physicians in Winnipeg, Manitoba, Canada. Each physician will enroll 30 patients attending their periodic health examination and at average risk for colorectal cancer. All physicians will follow their standard clinical practice for screening. Intervention group physicians will provide a fridge magnet to each patient that contains information facilitating access to the study-specific colorectal cancer screening decision aids (telephone help-line and website). The primary endpoint is patient fecal occult blood test completion rate after four months (intention to treat model). Multi-level analysis will include clinic, physician and patient level variables. Patient Personal Health Identification Numbers will be collected from those providing consent to facilitate analysis of repeat screening behavior. Secondary outcome data will be obtained through the Clinic Characterization Form, Patient Tracking Form, In-Clinic Patient Survey, Post-Study Follow-Up Patient Survey, and Family Physician Survey. Study protocol approved by The University of Manitoba Health Research Ethics Board.

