
**Figure 4 F4:**
[figure not shown]
**Flow Diagram of study protocol for family physicians. **Ψ, strata based on membership in the Physician Integrated Network (PIN) and/or Uniting Primary Care and Oncology Network (UPCON); blocked based on the number of family physicians per cluster.

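### The blocking factor, number of collaborating physicians, enters the model only as solo/group practice; if practice size predicts FOBT completion, the test is somewhat conservative and some power is lost

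*Protocol article*

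**What the plan says.** The protocol article, under Sample size determination, randomization, and statistical analysis, restricts the allocation in two ways:

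- Stratification: "clusters will be randomized within strata based on membership in the Physician Integrated Network (PIN) and/or Uniting Primary Care Oncology Network (UPCON").
- Blocking: "Clusters will be block randomized based on the number of collaborating FPs within a practice". The legend of Figure 4 repeats this: "blocked based on the number of family physicians per cluster".

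The same section specifies a "multi-level logistic regression that accounts for variance among patients with the same FP, FP within the same cluster, and among the clusters", fitted in GLIMMIX, and names the terms level by level. At cluster level they are "cluster level (treatment, electronic medical record or paper charts, PIN and/or UPCON membership"). At physician level they are "family physician level (gender, solo/group practice"). Patient-level covariates follow.

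The strata are therefore in the model. The number of collaborating physicians is not, except so far as solo versus group practice stands in for it.

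**The concern.** A factor that restricts the randomisation is balanced between arms by design, so the treatment estimate varies less from one allocation to the next. The analysis sees that gain only if it conditions on the factor. If the factor predicts outcome and is left out, its variance is counted as unexplained between-cluster variation. The reported standard error then exceeds the true sampling variability, the test rejects too seldom under the null, and power is lower than the design could give.

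Here the omission is partial. A solo/group indicator separates one-physician practices from the rest but treats all group practices alike. At stake is whatever prognostic information practice size carries beyond that split and the other listed covariates, in a trial with few clusters.

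**Working it through.** **Inputs from the article.** The Abstract gives "22 community-based family practice clinics (36 clusters) with 76 fee-for-service family physicians" and 30 patients per physician: 76/36 = 2.1 physicians and 76 × 30/36 = 63 patients per cluster on average. The article gives no figure for the association between practice size and FOBT completion, so there is no planned figure to reproduce on this point.

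**Step 1: formula.** Assume equal clusters of 63. Let R be the share of between-cluster variance that size explains beyond the terms already fitted. On the scale of cluster means, the omitted share of variance is

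r = R × ICC / [ICC + (1 − ICC)/63].

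The treatment-effect variance is overstated by 1/(1 − r). True type I error is 2[1 − Φ(1.96/√(1 − r))]. An analysis with 80% power when size is included has power Φ(2.80 − 1.96/√(1 − r)) when it is not.

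At an assumed ICC of 0.05 the denominator is 0.05 + 0.95/63 = 0.0651:

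| R (assumed) | r | Variance ratio | Type I error | Power |
|---|---|---|---|---|
| 0 | 0 | 1.00 | 0.050 | 80% |
| 0.1 | 0.077 | 1.08 | 0.041 | 78% |
| 0.2 | 0.154 | 1.18 | 0.033 | 75% |
| 0.3 | 0.230 | 1.30 | 0.026 | 72% |

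At the ICC of 0.6 used in the article's sample-size paragraph, the multiplier of R is 0.6/(0.6 + 0.4/63) = 0.99. R = 0.1 then gives r = 0.099 and power of about 77%; R = 0.3 gives r = 0.297 and about 68%.

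**Step 2: simulation with solo/group in the model.** Assumptions not in the article: 18 one-physician clusters and 18 with 2 to 6 physicians (8 of size 2, 4 of size 3, 2 each of sizes 4, 5 and 6; total 76); residual between-cluster SD of 0.35 on the logit scale; treatment effect of 0.45 logit; 1:1 allocation in size-ordered blocks of four; t-test on cluster proportions; 4000 runs per scenario. The size effect is in logit per SD of log size. Solo is taken to mean exactly one collaborating physician.

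| Size effect | Power: no size term | Power: solo/group | Power: log size | Type I: solo/group | Type I: log size |
|---|---|---|---|---|---|
| 0 | 79% | 79% | 79% | 4.9% | 4.9% |
| 0.15 | 78% | 80% | 81% | 5.4% | 5.5% |
| 0.30 | 67% | 77% | 80% | 4.1% | 4.9% |
| 0.45 | 51% | 74% | 80% | 3.3% | 5.3% |

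The Monte Carlo standard error of a 5% rate is √(0.05 × 0.95/4000) = 0.34 percentage points, so 5.4% and 5.5% are compatible with 5%. Before rounding, the strong-effect powers are 73.6% and 80.4%, a gap of 6.8 points.

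In null runs with solo/group fitted, the mean model standard error against the true SD of the estimate is 0.0364 vs 0.0364, 0.0366 vs 0.0367, 0.0376 vs 0.0363 and 0.0391 vs 0.0359. The overstatement is nil, nil, about 4% and about 9%.

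**Step 3: why the proxy recovers most of the loss.** In the assumed distribution the mean log size is 0.542 overall, 0 for solo and 1.084 for group. The sum of squares between solo and group is 36 × 0.542² = 10.58, out of a total of 13.54, so solo/group carries 78% of the variance of log size and leaves 22%. The leftover R, with residual variance 0.35² = 0.1225, is:

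- weak: 0.15² × 0.22 = 0.005; 0.005/(0.005 + 0.1225) = 4%
- moderate: 0.30² × 0.22 = 0.020; 0.020/(0.020 + 0.1225) = 14%
- strong: 0.45² × 0.22 = 0.045; 0.045/(0.045 + 0.1225) = 27%

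These shares fall within or below the range tabulated in step 1, and the simulated losses agree with it. In the strong case, size explains 0.45²/(0.45² + 0.35²) = 62% of all between-cluster variance before adjustment, which is a demanding assumption.

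**The case against.** The strongest reply is that practice size is not left out. Solo/group practice is in the model, and in the simulation it recovers most of what would be lost with no size term: 77% power against 80% at a moderate effect, where omitting size altogether gives 67%. The reply stands, and it limits the point to the residual information in the count.

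Secondly, nothing in the article shows that practice size is prognostic. The stated aim of balancing cluster characteristics is attached to the PIN/UPCON strata. The blocking could equally have been meant to equalise physician and patient numbers per arm. If size does not predict completion, nothing is lost. This stands too, and is why the point is conditional.

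Thirdly, the article is condensed, and coding of blocking factors can be left to an analysis plan. This carries less weight, because the article does state both its allocation factors and its model terms, and the two lists do not match. The list is not worded as exhaustive, so adding the factor would be consistent with the text.

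In the other direction, the proxy could be weaker than simulated. Blocking uses collaborating physicians, whereas solo/group is a practice type; a group practice with one participating physician is group in the model but size one for blocking. If half of the one-physician clusters were of that kind, a simulation of the same design gives power of 69% (moderate) and 56% (strong), against 80% with size included. A reader might infer a loss of that order, but the article does not say how often this happens, and the one-half is purely an assumption.

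**Conclusion.** The model does not fully match the randomisation: one restricting factor is included, and the other enters only in coarse form. If practice size predicts FOBT completion beyond solo/group and the other listed covariates, the standard error will be somewhat too large and the test conservative. The illustrative power loss is 0 to about 6 or 7 percentage points with solo/group fitted, and nil if size is not prognostic.

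A reader might infer that the error bars will certainly be too wide, or that the model ignores practice size. The article supports neither: a proxy is fitted, and no figure links size to outcome. Nor is there bias or type I inflation here; any error is on the conservative side.

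The magnitudes rest on an assumed size distribution, assumed size effects, an ICC of 0.05 in the main table, and cluster proportions in place of the three-level GLIMMIX model. Only the direction is firm. The change is still worth making because it costs so little.

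**What to change.** Add the number of collaborating physicians per cluster as a cluster-level fixed effect in the GLIMMIX model, alongside PIN/UPCON membership. Use the categories applied in the blocking or, to spare degrees of freedom with 36 clusters, a single count or log-count term. Drop solo/group if it then adds nothing, and name the chosen form before outcome data are seen.

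The value is known for every cluster at randomisation, so no data need collecting. The cost is a line of text and one or a few cluster-level degrees of freedom: one for a count term, more for several categories. In the simulation, the single log-count term cost no power when size was unrelated to outcome (79% either way).

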**Discussion:**

The study intervention has the potential to increase patient fecal occult blood test uptake, decrease colorectal cancer mortality and morbidity, and improve the health of Manitobans. If utilization of the website and/or telephone support line result in clinically significant increases in colorectal cancer screening uptake, changes in screening at the policy- and system-level may be warranted.

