The first point of contact for a majority of patients seeking healthcare is with a community-based family physician. Family physicians play a key role in quality healthcare delivery, including CRC screening [19]. Manitobans depend on their family physicians to inform them of the need for FOBT testing in the prevention of CRC [8]. Physicians estimate it takes approximately four minutes to do a good job of explaining CRC and relevant screening options [20]. This represents between 27 and 40% of the total time available during the periodic health examination. In 2005, a study by Stokamer et al. demonstrated an increase in FOBT compliance from 51.3% to 65.9% using intensive one-on-one CRC education by registered nurses that took an additional 4.6 minutes beyond the time of standard CRC screening patient education (consisting of written instructions for the FOBT and verbal instruction to return the completed test within two weeks) [20]. Family physicians require supportive tools to facilitate FOBT recommendation and compliance among their patients to improve overall FOBT screening rates. Research is required to identify innovative methods of supporting family physicians in their role in CRC screening. Developing strategies aimed at supporting both the primary care provider as well as their patients has the potential to lead to substantial improvements in FOBT screening rates. Patient education about CRC and the importance of screening has been demonstrated to improve patient knowledge and compliance with FOBT [20,21]. Substantial improvements in FOBT completion rates have been demonstrated by studies that emphasized the importance of the FOBT, increased patient confidence in their ability to complete the FOBT, taught patients how to do the test, and provided time for patients to ask and receive answers to their individual questions about CRC and the FOBT [20]. Intervention strategies resulting in higher completion rates commonly involve one-on-one patient contact in clinics by registered nurses which is costly, time consuming [20], and uncommon in most community-based fee-for-service clinical practices in Manitoba. It may be more cost-effective to utilize a less expensive strategy, specifically a telephone support line managed by registered nurses. Another alternative may also involve access to a website with CRC information and FOBT assistance for patients. Although personalized emails from a physician reminding patients to undergo CRC screening and provided a link to a webpage with information about CRC did not improve FOBT compliance among patients [22], a multimedia educational computer program was demonstrated to be as effective as usual nurse counseling in educating patients and achieving adherence to FOBT screening [23].

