### Benefits

There are a number of benefits of the study protocol which are outlined as follows:

(1) The pragmatic design and flexibility of the protocol for each medical practice ensured it reflected the “real world” clinical practice environment and its inherent variability. This approach will produce findings that are generalizable and relevant to community-based family practice and will increase translation and application of evidence-based findings into the clinical practice setting. The study was powered to detect an absolute increase in CRC screening rates of 15% by the intervention. This is a realistic and clinically significant improvement.

(2) The multi-disciplinary team working together on this project represent multiple stakeholder opinions and contributions (primary care providers, primary care researchers, policy makers, and patients). It also reflects a variety of providers/practitioners all of which enhance the pragmatic nature of the design and findings. Working collaboratively on this research project facilitated creation of new networking opportunities and partnerships that have the potential to support future primary healthcare research that inform evidence-based family practice.

(3) Findings will allow us to describe the degree of variability in screening rates among the medical clinics and practitioners involved in the study and, the rates of internet usage among the age category 50–74 for a health-related issue, and more specifically, CRC information and screening.

(4) Findings will provide valuable patient feedback about the FOBT and the common issues related to completion/non-compliance with the test.

(5) The study is highly representative of the community-based clinical practice environment and included a variety of FPs from a number of different areas in the city and practice settings.

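### The 15-point target is sized as a difference between users and non-users of the aid but presented as the effect of the intervention; at 20% use it implies only about 3 or 6 points for the primary comparison by arm

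*Protocol article*

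**What the plan says.** All references are to the protocol article.

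- **Clinical significance** (Sample size determination, randomization, and statistical analysis): "An absolute increase in FOBT screening rates of 15% from the current 42% in Manitoba will be considered clinically significant". The 42% is a provincial screening rate, so the sentence reads as a statement about a whole group of patients. No other figure for clinical significance is given.
- **Sizing** (same paragraph): 41 clusters of 30 to 35 patients, with 80% of observations in a non-using group, while "20% are in the group that does utilize the intervention/magnet; 1230 observations". The claim made for this split is that it "will achieve 90% power at a 0.05 significance level to detect a change from the baseline value of 0.400 to 0.550". The odds ratio is printed as 1.833. The two groups in this calculation are users and non-users.
- **Primary result** (Primary outcome, and the analysis text of the sample-size section): the proportion completing within four months in each group, analysed by intention to treat with a multi-level logistic model. Use of the telephone line or website is left to the patient (Experimental treatment group). The Primary outcome section also plans to look at completion among those who accessed the aids, against control patients.
- **Benefits**: the trial is said to have power for a 15-point absolute rise in screening brought about by the intervention, followed by "This is a realistic and clinically significant improvement".
- **Conclusion** (Discussion part of the Abstract, with a parallel sentence in the main Discussion): if use of the website or telephone line should "result in clinically significant increases in colorectal cancer screening uptake, changes in screening at the policy- and system-level may be warranted".

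**The concern.** One figure, 15 points, serves two different contrasts. In the sizing it separates users from non-users. In the clinical-significance sentence and the Benefits section it is a rise in the screening rate caused by offering the aid. The two coincide only if nearly everyone offered the aid uses it, and the sizing assumes that most will not.

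The primary analysis compares everyone given a magnet with everyone in the control arm. A gain confined to users is diluted there by the share who use the aid. A reader of the Benefits section would expect a rise of about 15 points between arms and would take the trial to be sized for it, whereas the plan's own inputs describe a much smaller arm-level rise. The trial's result could then be judged against a figure that belongs to a different comparison.

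**Working it through.** **Inputs.** Baseline 0.40 (sizing) or 0.42 (clinical-significance sentence); rise of 0.15; use 20%; 1230 observations; cited nurse-education study 51.3% to 65.9% (Background). Assumptions: the aid changes completion only in those who use it, users would otherwise complete at the average rate, and allocation is 1:1 by patient.

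**The plan's own figures.**
- Observations: 41 × 30 = 1230 and 28 × 30 = 840. Both agree.
- Odds ratio: (0.55/0.45) / (0.40/0.60) = 1.833. It agrees.
- Power, two-sided, users against non-users at 20/80: 98.9% (1230) and 93.9% (840) without clustering. Reading the 0.6 as a correlation in a logistic-regression formula, so that R² = 0.36, gives 92.5% and 80.2%. R² = 0.40 gives 90.8% and 77.6%. A design effect of 1 + 29 × 0.6 = 18.4 gives 16.7% and 12.7%. No variant tried yields both printed figures, 90% and 80%. The argument below does not use the power.

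**What the 20% is a share of.** The text does not say.
- Reading A: 20% of the intervention arm.
- Reading B: 20% of all 1230 observations, i.e. 246 users. In an arm of 615 that is 246/615 = 40%. This is the more literal reading: the percentages are attached to the 1230 observations, and the Abstract gives 36 clusters for the whole trial, so 41 looks like a whole-trial number.

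**Formulas.** With use share *u* in the intervention arm and baseline *p*:
- arm-level rise = *u* × (gain in users)
- ceiling, if every user completes = *u* × (1 − *p*)
- completion among users needed for a 15-point arm-level rise = *p* + 0.15/*u*

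| | Reading A, *u* = 0.20 | Reading B, *u* = 0.40 |
|---|---|---|
| Rise if users gain 15 points | 0.20 × 0.15 = 3.0 points | 0.40 × 0.15 = 6.0 points |
| Ceiling from 42% | 0.20 × 0.58 = 11.6 points | 0.40 × 0.58 = 23.2 points |
| Ceiling from 40% | 0.20 × 0.60 = 12.0 points | 0.40 × 0.60 = 24.0 points |
| User completion needed, from 42% | 0.42 + 0.75 = 117% (impossible) | 0.42 + 0.375 = 79.5% |
| User completion needed, from 40% | 0.40 + 0.75 = 115% (impossible) | 0.40 + 0.375 = 77.5% |

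**Comparison with the cited evidence.** On reading B users must gain 37.5 points. The Background cites a study that "demonstrated an increase in FOBT compliance from 51.3% to 65.9% using intensive one-on-one CRC education by registered nurses", a gain of 65.9 − 51.3 = 14.6 points from face-to-face teaching.

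**Where 15 points becomes possible.** With every user completing, use in the intervention arm must be at least 0.15/0.58 = 25.9% (from 42%) or 0.15/0.60 = 25.0% (from 40%). At 20% use, users would otherwise have to complete at 25% or less, since 0.20 × (1 − 0.25) = 0.15.

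**The case against.** A reader might go further and infer that the 15-point rise can never be reached, so that even a fully effective aid would be declared not clinically significant and would lose its case for policy change. The protocol does not support that:

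- On reading B the ceiling is 23.2 to 24.0 points, so 15 is demanding but attainable.
- The protocol says that a 15-point rise counts as clinically significant. It nowhere says that a smaller rise will be declared not so. Working out how often an observed rise would pass 15 points tests a rule that the protocol does not contain.
- The policy sentences speak of use of the aids, repeat no number, and say only that change may be warranted. They could be read as referring to users.
- The magnet might prompt patients who never call or log on: the Background draws on a model with cues to action and lists forgetting as a reason for not completing. Users might also start from a lower rate than average. Either would raise the arm-level figure.
- The 14.6-point gain in the cited study gives some basis for the size of 15 points. The 15 points from 42% also comes first in the text with its own citation, so it cannot be said to have been carried over from the sizing.

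All of this stands, and it limits the point to an inconsistency. It does not remove it. If the 15 points was meant for users, the Benefits section misdescribes it as the effect of the intervention, and setting users against control patients is not a randomized comparison. If it was meant for arms, it does not match the contrast that was sized. Support from the cited study is for patients who actually received the teaching, not for a whole arm in which most do not use the aid.

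**Conclusion.** The point holds as an inconsistency between the stated target and the primary contrast. On the protocol's own use figure, the effect assumed in the sizing corresponds to an arm-level rise of about 3 points (reading A) or 6 points (reading B), not 15. An arm-level rise of 15 points is out of reach on reading A and needs roughly double the baseline completion among users on reading B. Calling it realistic for the intervention is therefore not supported by the plan's inputs. The figures rest on no effect of the magnet in non-users; reading B also rests on 1:1 allocation, and the ceilings and required user rates on average baseline completion in users. The conclusion does not depend on the stated power, and repairing the power would not remove it. It does not extend to saying that the trial is bound to report a result that is not clinically significant.

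**What to change.** 1. **Sample-size section.** State that 0.400 to 0.550 is a contrast of users with non-users, say what the 20% is a share of, and put the implied arm-level intention-to-treat rise next to it (3 or 6 points, according to the denominator).
2. **Benefits section.** Remove or correct the statement that the trial has power for a 15-point rise due to the intervention, and drop the claim that such a rise is realistic at arm level.
3. **Discussion, in the Abstract and main text.** Rest the conclusion about the intervention on the arm difference from the planned clustered model with its 95% confidence interval. Label the comparison of users with control patients as non-randomized.
4. **Clinical importance.** Keep any threshold as a separately justified judgement, tied explicitly to the difference between arms. It should not be set to 3 or 6 points merely because expected use implies those figures: how large a rise matters does not follow from how many patients are expected to use the aid.

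Items 1 to 3 are wording changes and need no new patients or data; item 4 needs a stated justification. The cost is that the stated target effect becomes less favourable.
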